### Statistical analysis

Descriptive statistics will be presented as the means and standard deviation (SD), proportions, and medians with interquartile ranges where appropriate. In the efficacy analyses for blood pressure, mixed-effects model repeated measures will be used to compare the changes in BP for people on the hypertension registers (i.e. with a clinical code for hypertension) between one year before and one year after implementation of the digital intervention within each practice. Fixed effects in the model are the exposure, whether BPs are measured (home or clinic), periods (12 months before and after implementation), interaction terms between the exposure and time period variable and covariates that were selected a priori because they have been reported to show correlations with both BP and cardiovascular (CVD) risk and could potentially confound the association between BP and CVD risk. These potential confounders will include baseline demographic characteristics (age, sex, ethnicity, IMD and frailty), clinical characteristics at baseline (SBP and DBP, total cholesterol, smoking, antihypertensive medication use), past history (diabetes, established cardiovascular disease, and chronic kidney disease). Random effects for patient and practice level average BP will also be included in the model. These covariates were selected a priori because they have been reported to show correlations with both BP and CVD risk and could potentially confound the association between BP and CVD risk [12]. Covariates are defined using the closest available electronic healthcare records data prior to baseline. The intervention analysis will take a similar approach albeit limited to the self-monitoring group and the variables included in the Hypertension-Plus dataset.

A 5% significance level will be used for all analyses/ tests.

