### The intervention

The digital intervention (“Hypertension Plus”) was provided by Omron Healthcare combining blood pressure telemonitoring with prompts for hypertension management including medication titration intended to facilitate remote care [4]. The intervention is based on workflow algorithms developed from research data and decision support tools designed to be compliant with National Institute for Health and Care Excellence (NICE) guidelines [8].

The system combines a web-based dashboard for professionals, which both reads and writes data to the practice clinical system, with a mobile phone “app” which is downloaded by participating patients and used to upload BP readings. Patients are invited to use the digital intervention via contact from their practice and then sign up via a bespoke web interface. The choice of which patients receive an invitation is at the discretion of practices, but they are typically people with raised BP receiving antihypertensive treatment plus some without a diagnosis of hypertension. Telephone and online support is provided for those people having problems accessing or engaging with the technological platforms.

The digital intervention is a commercial system and is licenced annually, usually at local healthcare organisation level (known as primary care networks (PCN) or Integrated Care Boards in England). Implementation is being led by Omron working with the National Association for Primary Care (NAPC, https://napc.co.uk) and includes training for practices, support with identification of appropriate groups, support for patients, and peer led support facilitated by the NAPC.

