### Quantitative study

Pseudonymised coded and numeric clinical data will be extracted using the Oxford-Royal College of General Practitioners Clinical Informatics Digital Hub (ORCHID) system [7]. ORCHID is a secure system that regularly extracts pseudonymised data from member practices for disease surveillance, quality improvement and research purposes (https://orchid.phc.ox.ac.uk/index.php/orchid-data/). Data will not be extracted from records of patients who have opted out of use of their health records in research. The analysis will take place within the ORCHID trusted research environment. Outside of ethically approved trials with individual consent, no individual data leaves this network. All aggregate data extracts subject to statistical disclosure control.

People invited to use the digital intervention will be compared to patients on the practice hypertension register who have not been invited. Outcomes will be assessed using predefined curated variables of Systematised Nomenclature of Medicine (SNOMED) clinical terms (CT) codes (Fig. 1; see https://github.com/[name] for codelists) [9].

(Fig. 1)

The most recent routinely collected retrospective data extracted at baseline will include:

Age (years).Sex.Ethnicity.Smoking status.Index of Multiple Deprivation (IMD), a measure of socioeconomic status.Height, weight, body mass index (kg/m2).Total and HDL cholesterol (mmol/L).Systolic and diastolic blood pressure (clinic and/or home readings).Pulse.Past medical history:Diagnosis of diabetes (Type 1 or 2).Previous myocardial infarction or stroke.Diagnosis of chronic kidney disease.Medication useStatin treatment (drug type and dose).Antihypertensive medication use.Other current cardiovascular medication.Electronic Frailty Index (eFI) and/or characteristics required to calculate this.Health Economic Resource use: relevant consultations, referrals and admissions as available.Practice identifier (pseudonymised).

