### Outcomes

### Primary outcome

The primary outcome will be change in systolic blood pressure (SBP, clinic and home BP both included) in mmHg extracted from the electronic healthcare record comparing 12 months before and after intervention implementation along with comparison between those on the hypertension register invited to use and not invited to use the intervention.

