### Sample size

Sample size requirements for this study were determined through simulation. A mean BP of 148 mm Hg was assumed, with practice variation (standard deviation, SD) of 5 mm Hg. Within a practice, patient variation (SD) was assumed as 17 mm Hg and measurements within a patient were assumed to vary by 10 mm Hg (SD) about the patient mean. Effect size was assumed to be -3 mm Hg (BP 3 mm Hg lower in patients using the digital intervention) and a minimum of 4 BP measurements for each patient. This demonstrated that to achieve 90% power at the 5% significance level, 100 patients each drawn from 8 general practices would be required for this study (800 patients in total, 91% power). Assuming greater variation (practice SD = 10 mm Hg, patient SD = 22 mm Hg or measurement SD = 14 mm Hg), the required sample size was 100 patients from 14 practices respectively. The available sample will depend upon the implementation rate as well as recruitment and will include as many patient records as are available.

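### The before/after split is dated by practice but exposure begins patient by patient, so readings taken before an invitation can count as exposed

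*Protocol article*

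**What the plan says.** Time is set at practice level. In the protocol article, Statistical analysis, BP is compared "between one year before and one year after implementation of the digital intervention within each practice", and the fixed effects include "periods (12 months before and after implementation), interaction terms between the exposure and time period variable". The Primary outcome section uses the same window: "comparing 12 months before and after intervention implementation along with comparison between those on the hypertension register invited to use and not invited".

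Exposure is set at patient level. The Quantitative study section states: "People invited to use the digital intervention will be compared to patients on the practice hypertension register who have not been invited". The section on the intervention describes how a person comes to be exposed: "Patients are invited to use the digital intervention via contact from their practice and then sign up via a bespoke web interface". It adds: "The choice of which patients receive an invitation is at the discretion of practices", and notes that those chosen typically have raised BP.

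No patient-level start date is given for the health-record analysis. Only the separate analysis of the Hypertension-Plus database starts from each patient's own first measurements. The article does not say when invitations go out relative to implementation, and it does not define the implementation date. The Sample size section assumes −3 mm Hg for patients using the system.

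**The concern.** The group variable describes something that happens to a person on a particular day, while the period variable changes for everyone in a practice at once. A patient invited some months after implementation spends those months in usual care, yet every reading from them enters the model as exposed and after. The −3 mm Hg on which the study is powered cannot be present in that time.

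Group membership is also fixed by a later event. If a high reading after implementation prompts the invitation, that reading is itself counted as an exposed outcome.

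The exposure-by-period interaction carries the primary comparison. If the lag is appreciable, this coefficient is not the effect of being invited, and a reader who takes it as such would tend, on this account alone, to understate the benefit.

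**Working it through.** **Inputs from the article (Sample size, Statistical analysis).** Effect −3 mm Hg; SDs of 5 (practice), 17 (patient) and 10 mm Hg (measurement); at least 4 readings per patient; 8 practices × 100 = 800 patients; stated power 91%; 5% level, taken here as two-sided. **Assumed, because not given:** the lag from implementation to invitation, and the reading rate before and after invitation.

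**The stated 91%.** Power = Φ(3/SE − 1.96).
- Parallel groups, 400 v 400, mean of 4 readings: SD = √(17² + 10²/4) = 17.72, power 66.8%. With 800 v 800 it is 92.3%, or 90.3% with the practice SD included.
- Difference in differences, 2 readings before and 2 after: SD of change = 10√(1/2 + 1/2) = 10. Power is 98.9% for 400 v 400, and 92.4% if 20% of the 800 are invited.

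The article does not give the group split, the split of readings or the simulated model. So 91% can be approached in several ways but not uniquely reproduced, and it is not shown to be wrong.

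**Dilution.** If a share f of invited patients' after-year readings precede invitation, the interaction becomes −3(1 − f). With equal reading rates and invitations uniform over the first u months, the mean wait is u/2 of 12 months, so f = u/24. The SE implied by 91% is 3/(1.96 + 1.34) = 0.909. The patients needed to hold 91% are 800/(1 − f)², ignoring any limit set by the number of practices.

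| u (months) | f | Term (mm Hg) | Power at SE 0.909 | N for 91% |
|---|---|---|---|---|
| 0 | 0 | −3.00 | 91% | 800 |
| 1 | 0.042 | −2.88 | 88.6% | 872 |
| 3 | 0.125 | −2.63 | 82.3% | 1,045 |
| 6 | 0.250 | −2.25 | 69.7% | 1,423 |
| 12 | 0.500 | −1.50 | 37.8% | 3,200 |

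The power column depends on that SE. Under the 400 v 400 difference-in-differences set-up the same rows give 98.9%, 98.2%, 96.0%, 88.9% and 56.4%.

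**Simulation check** (difference in differences, 1,500 runs per setting). The practice-date split returned −2.99, −2.61, −2.22 and −1.50 mm Hg for u = 0, 3, 6 and 12. Splitting at the patient's own date returned about −3.0 throughout.

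**Extra readings after invitation.** Simulated terms from a repeated-readings model, in mm Hg:

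| Readings | u = 3 | u = 6 | u = 12 |
|---|---|---|---|
| 4 a year, plus 4 a year after invitation | −2.72 | −2.58 | about −2.0 |
| 2 a year, plus 10 a year after invitation | −2.96 | −2.84 | about −2.4 |

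The Monte Carlo error is about 0.05 to 0.07 for the 3- and 6-month columns.

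**Invitation prompted by a reading.** With an assumed rule that a reading of 150 mm Hg or more after implementation prompts the invitation, the practice-date split returned −0.8 to −1.3. Individual index dates without control for earlier BP returned −1.5 to −1.8. Neither recovers −3.

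**The case against.** A reader might infer that the primary estimate is biased towards no effect and that the practice-date anchor must be replaced. The documents support neither.

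- **Staggered invitation is not documented.** The article says who chooses the invitees, not when they are contacted. References elsewhere to an implementation rate and an implementation period hint at a spread but do not establish one. If all invitations go out at once, nothing is lost.
- **The largest loss needs equal reading rates.** The system writes to the practice record and home readings count in the outcome, so extra readings after invitation are plausible. They reduce f.
- **The net direction is open.** If people are invited because of raised readings before implementation, regression to the mean exaggerates their fall and makes the estimate too favourable. If the prompting reading falls after implementation, it works the other way.
- **Dating from invitation has its own bias.** It ties time zero to a decision driven by BP, as the prompted-invitation result shows. The practice date does not depend on any one patient's BP, and it is the only date that invited and uninvited patients share.
- **The practice anchor suits a service evaluation.** What happened in the first year of rollout, lag included, is a fair question.
- **The dates may be fixed elsewhere.** Fig. 1 or a fuller plan may define them.

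All of this stands against a claim of net dilution and against swapping the primary anchor. It does not remove the mismatch: as the article states the rule, any reading between implementation and invitation is classed as exposed.

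**Conclusion.** The point holds as a misclassification built into the stated rule. Taken alone, it shrinks the interaction by the factor 1 − f. The size is conditional: with a true −3 mm Hg it runs from no loss (immediate invitation) to half the effect (invitations uniform over the full year at equal reading rates). A three-month spread costs about 0.4 mm Hg at equal rates and almost nothing if post-invitation readings are much more frequent.

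The overall bias of the primary estimate cannot be signed from the article. Invited patients who never sign up are a further source of dilution that no choice of invitation date removes. The practice-date contrast can stay, provided it is read as a first-year rollout effect and is accompanied by a prespecified analysis that dates exposure correctly.

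**What to change.** 1. Define the practice implementation date, and report the distribution of the lag from it to each invitation.
2. Beside the practice-date split, prespecify an analysis in which exposure starts at the patient's own invitation or sign-up, naming which. Either use a time-varying exposure, with invited patients' pre-invitation readings coded as unexposed, or give uninvited patients index dates drawn from the invitation dates in the same practice and compare the 12 months either side.
3. Leave out the reading on the index date, which may have prompted the invitation, and adjust for or match on pre-index BP. Baseline BP is already a listed covariate. As a main effect alone it shifts both periods equally, so it should be entered in a way that can act on the change, for example in interaction with period.
4. State that the practice-date estimate is a first-year rollout effect, not the effect of being invited.

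**Cost.** Analysis code, a paragraph of text and a dated invitation or sign-up record. The article does not describe such a field, so its availability in the extract must be confirmed. The time-varying version fits the existing window. A full 12 months after each index date needs an extract reaching 12 months past the last invitation used. The invitation-dated estimate remains open to residual regression to the mean, so the two analyses should be reported together.

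### The primary model fits one before/after shift for all practices, so practice-specific BP change can leak into the invited-versus-uninvited estimate if invited shares differ between practices

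*Protocol article*

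**What the plan says.** In the protocol article, Statistical analysis, changes in BP among people on the hypertension registers are compared "between one year before and one year after implementation of the digital intervention within each practice". The fixed effects listed are exposure, home or clinic measurement, period, exposure x period, and patient covariates. On clustering the text says "Random effects for patient and practice level average BP will also be included in the model". Practices may thus differ in level, but no listed term lets the before/after change differ by practice.

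Under The intervention, "The choice of which patients receive an invitation is at the discretion of practices". Under Quantitative study and Primary outcome, the contrast is invited against not invited patients on the register. The primary outcome also includes the before/after change itself. Under Sample size, the only practice variation assumed is in mean level. Secondary outcomes use the same comparison for DBP, and the Subgroups section repeats the models.

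**The concern.** With one common period effect, the exposure x period estimate is the pooled change in invited patients minus the pooled change in uninvited patients. If one practice invites many patients and another few, the invited group is weighted towards the first practice. Whatever moved BP there for everyone (a change in recording, in hypertension care, or in the calendar months that its windows cover) is then partly read as an effect of the invitation.

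Two consequences follow when shares differ. Even if practice shifts are unrelated to shares, the model ignores a source of variance in its primary contrast, and the confidence interval is too narrow. If shifts and shares are related, for example because an engaged practice both invites more and improves care generally, the point estimate is biased. That can create an apparent benefit or hide a real one.

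**Working it through.** **Inputs from the article.** Effect: "Effect size was assumed to be -3 mm Hg". Practice level: "with practice variation (standard deviation, SD) of 5 mm Hg". Patients: "patient variation (SD) was assumed as 17 mm Hg". Measurement SD within a patient is 10 mm Hg, with at least 4 readings. Size: "100 patients each drawn from 8 general practices would be required for this study (800 patients in total, 91% power". Test level: "A 5% significance level will be used for all analyses/ tests", taken here as two-sided.

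**Inputs not in the article, assumed.** Two readings before and two after; invited shares p of 10-60% (0.10, 0.15, 0.20, 0.30, 0.40, 0.50, 0.55, 0.60) or 20-40% (evenly spaced); practice shifts s of SD 1 to 3 mm Hg; correlation between shift and share of 0 or magnitude 0.5.

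**The plan's own figure.** The 91% cannot be uniquely reproduced, because the invited share and the split of readings in the simulation are not stated. The variance of a patient's change is 100 x (1/2 + 1/2) = 100. A comparison of changes in 800 patients gives:
- 50% invited: SE = 10 x sqrt(1/400 + 1/400) = 0.707, power 98.9%.
- 20% invited: SE = 10 x sqrt(1/160 + 1/640) = 0.884, power 92.4%.

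The point does not depend on which design was simulated.

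**Bias.** With a patient random intercept and balanced readings, the estimate equals the difference in mean change, so

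bias = cov(s, p) / [p̄(1 - p̄)] = correlation x SD(s) x SD(p) / [p̄(1 - p̄)].

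- Shares 10-60%: p̄ = 0.35, SD(p) = 0.179, p̄(1 - p̄) = 0.2275. At correlation magnitude 0.5 and shift SD 2: 0.5 x 2 x 0.179 / 0.2275 = 0.8 mm Hg. At shift SD 3: 1.2 mm Hg.
- Shares 20-40%: p̄ = 0.30, SD(p) = 0.0655, p̄(1 - p̄) = 0.21. At shift SD 1: 0.5 x 1 x 0.0655 / 0.21 = 0.16 mm Hg. At shift SD 2: 0.31 mm Hg.

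The sign is that of the correlation. Simulation with a true effect of zero and the bias towards benefit gives -0.78 and -1.17 mm Hg for the wide shares, with rejection in 22% and 38% of runs. The narrow shares give about -0.2 and -0.3 mm Hg, with rejection in 6-8%.

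**Standard error at zero correlation.** The shifts add a component to the estimate with

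SD = SD(s) x SD(p) / [sqrt(8) x p̄(1 - p̄)].

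For the wide shares this is 0.179 / (2.83 x 0.2275) = 0.278 per mm Hg of shift SD. The SE without shifts is 10 x sqrt(1/280 + 1/520) = 0.741. The model reports slightly more, because the shifts also enlarge the residual variance.

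| Shift SD | True SD of estimate | SE the model reports (approx.) | Type I error (approx.) |
|---|---|---|---|
| 1 | sqrt(0.549 + 0.077) = 0.79 | 0.741 x sqrt(1.01) = 0.745 | 6% |
| 2 | sqrt(0.549 + 0.308) = 0.93 | 0.741 x sqrt(1.04) = 0.756 | 11% |
| 3 | sqrt(0.549 + 0.692) = 1.11 | 0.741 x sqrt(1.09) = 0.774 | 17% |

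Simulation gives 11.9% and 17.6% for SD 2 and 3. For the narrow shares the added component is only 0.0655 / (2.83 x 0.21) = 0.110 per mm Hg, and the error is at most about 6%, close to nominal.

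**Equal shares.** With 30% invited everywhere, SD(p) = 0: there is no bias, and simulated type I error is 4-5%.

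**More practices.** With shares 10-50%, shift SD 2 and correlation magnitude 0.5, bias is 0.66 mm Hg with 8 practices and 0.58 with 14. Type I error is 15.5% and 18.7%. Extra practices do not cure it.

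**With fixed practice x period terms.** Simulated bias from this source is about 0 and type I error 4-6%. In the wide example the sum of 100 x p(1 - p) over practices is 156.5, so SE = 10 / sqrt(156.5) = 0.80 against 0.74, a rise of 8%.

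**The case against.** A reader might infer that the article promises a comparison of invited and uninvited patients inside each practice and then contradicts itself. The text does not support that firmly: the phrase on practices may only say that the windows are dated from each practice's own start. The point rests on the listed model terms.

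A reader might also infer that practice-wide change will be counted as intervention effect. The article says that practices choose which patients to invite. Different proportions are a natural consequence but are not stated, and nothing documents a practice-wide shift or a link between shift and share. Two practices inviting 60% and 10%, with shifts of -5 and 0 mm Hg, would give -0.625 / 0.2275 = -2.7 mm Hg, but that is an illustration chosen to be large.

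It is fair to say that a random practice-by-period effect would do most of the work. For the wide shares at correlation magnitude 0.5, it cuts the bias from -0.76 to -0.28 (shift SD 2) and from -1.19 to -0.25 mm Hg (SD 3), with rejection down to 7-8%. It is also fair that training practices is part of the roll-out, so some practice-wide change may be a real benefit that the fix removes from the contrast.

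The reply that random-effects detail belongs in an unseen analysis plan is weaker. The article spells out both the fixed and the random terms, and the omission follows from that list.

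**Conclusion.** The point holds conditionally. As listed, the model leaves practice-specific before/after change unmodelled in its primary contrast. If invited shares differ, the standard error is too small: type I error is about 6% to 18% at zero correlation over the assumed ranges, with the narrow shares near nominal. If shares are also associated with practice-wide change, the estimate is off by about 0.2 to 1.2 mm Hg at correlation magnitude 0.5, in either direction, against a planned 3 mm Hg. If shares are equal, nothing is lost. The actual size cannot be known from the article.

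Because the mechanism is conditional and its inputs undocumented, this is a should-fix rather than a fatal flaw. The remedy also does not make the comparison unbiased overall. The near-zero bias shown for it comes from simulations in which invitation is random within a practice, whereas the article says that those invited are typically people with raised BP. Confounding and regression to the mean from that selection remain.

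**What to change.** Add practice x period terms to the SBP model, preferably fixed (practice indicator interacted with before/after), so that the exposure x period effect comes from invited and uninvited patients of the same practice over the same windows. Carry the same terms into the DBP and subgroup models. An acceptable alternative is a random practice-by-period effect, ideally with the practice's invited share x period as a fixed term.

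Report the overall before/after change, which is part of the primary outcome, as the average of the practice-specific changes. State that any practice-wide benefit of implementation is excluded from the invited-versus-uninvited contrast and appears only in that average.

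The cost is a sentence in the analysis section and one parameter per practice. No new data are needed, since the pseudonymised practice identifier is already extracted. The standard error rises by about 8% in the wide-share example and less when shares are closer together. With 8 x 100 patients, simulated power for -3 mm Hg stays at about 96-97% under assumed shares of 10-50% or 10-80%.

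### The covariates are justified as confounders of BP with CVD risk and, on the plain reading, enter as main effects that remove little or none of the bias from different BP trends in invited and uninvited patients

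*Protocol article*

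**What the plan says.** In the protocol article, the Primary outcome section defines the outcome as SBP change from the 12 months before to the 12 months after implementation, "along with comparison between those on the hypertension register invited to use and not invited to use the intervention". With the model in Statistical analysis, the quantity that answers this is the exposure × period interaction.

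Statistical analysis lists fixed effects for exposure, home or clinic reading, period, and "interaction terms between the exposure and time period variable and covariates that were selected a priori". It adds random effects for patient and practice average BP. The reason for choosing the covariates is given twice: they correlate with both BP and CVD risk and "could potentially confound the association between BP and CVD risk".

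The list covers "baseline demographic characteristics (age, sex, ethnicity, IMD and frailty"), "clinical characteristics at baseline (SBP and DBP, total cholesterol, smoking, antihypertensive medication use") and a history of diabetes, cardiovascular disease and chronic kidney disease. On timing: "Covariates are defined using the closest available electronic healthcare records data prior to baseline". Each patient therefore has one value of each covariate for both periods.

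The intervention section leaves the choice of whom to invite to each practice. It says that those invited typically have raised BP and are on treatment, and that use requires a phone app.

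**The concern.** There are two linked faults.

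First, the selection criterion belongs to another question. A variable confounds this comparison if it is related to being invited and to how BP changes over the two years. The stated criterion mentions neither.

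Second, the form of entry matters more than the list. Exposure × period with patient intercepts already removes stable differences in BP level between invited and uninvited patients. What it leaves is a difference in background trend: for example, if younger or less frail patients are invited more often and their BP would have moved differently anyway. A covariate with one value per patient, entered as a main effect, describes BP level and not trend. It therefore cannot act on this remaining bias.

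The comparison is not randomised, and covariate adjustment is the main stated guard against confounding by invitation. A reader would take the reported estimate as adjusted for age, frailty, deprivation and treatment, when the bias from different trends by those variables is largely still in it.

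**Working it through.** **Plan's own figure.** The document gives no figure for this bias. Its 91% power for 800 patients (Sample size) does not bear on the point. The figure can be reached only under an allocation that is not stated (for example 92.4% for exposure × period with two readings before, two after and 20% invited), so it is neither confirmed nor contradicted.

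**Inputs from Sample size.** Mean 148 mm Hg, practice SD 5, patient SD 17, measurement SD 10, effect -3 mm Hg, at least 4 readings per patient, 8 practices of 100 patients. The imbalance between groups and the covariate-related trend are not given and are assumed below.

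**Step 1, algebra.** For patient i in period P (0 before, 1 after), with invitation E and pre-baseline covariate z, the plain reading is

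BP = a + bE + cP + δ(E×P) + θz + patient intercept + practice intercept + error.

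The patient's mean change is c + δE + error: θz and both intercepts cancel. Now let background change depend on z by τ mm Hg per SD, and let the groups differ in z by d SD. The invited-minus-uninvited difference in mean change is then δ + τd. The term θz cannot absorb τd; a z×P term can.

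**Step 2, size under assumptions.** Bias = τ × d.
- Low: 1 × 0.5 = 0.5 mm Hg, or 0.5/3 = 17% of the planned effect.
- High: 2 × 1 = 2.0 mm Hg, or 2.0/3 = 67%.

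**Step 3, simulation with a true effect of 0.** There were 8 × 100 patients, the SDs above and 150 runs per scenario. Invitation was driven by a covariate with τ = -2 mm Hg per SD. The fits were random-intercept models. Mean estimates of exposure × period (mm Hg):

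| Readings | No covariates | Main effects | Covariate × period added |
|---|---|---|---|
| 2 before, 2 after | -1.69 | -1.69 | 0.00 |
| Uneven counts | -1.59 | -1.58 | 0.04 |
| Uneven, some without an after reading | -1.63 | -1.64 | 0.00 |
| Uneven, more without an after reading (up to about 40%) | -1.58 | -1.56 | -0.07 |

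With balanced readings the first two columns agreed in every run. With uneven readings the largest shift in a single dataset was 0.27 to 0.81 mm Hg in these scenarios, but the average shift was at most 0.02.

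**Step 4, second check.** Random-intercept GLS with Poisson reading counts, 1500 patients and 150 simulations, for three settings within the assumed range. No covariates: -0.48, -0.99, -2.02. Main effect: -0.55, -0.93, -2.02. Covariate × period: 0.05, -0.08, 0.12 (simulation SE 0.06).

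**Step 5, what does move the contrast.** The home/clinic term varies between readings. Assume a 5 mm Hg home–clinic gap and after-period home shares of 80% (invited) and 20% (uninvited), with 15% in both groups before. Adding the term moved the estimate from -4.64 to -1.64. That matches 5 × (0.80 - 0.20) = 3.0.

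A scenario in which invitation follows a raised last reading gave a larger bias (-3.59). That is regression to the mean, a separate matter, and it is not counted here.

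**The case against.** **The parameterisation is not settled by the text.** The section never says main effects, and the sentence on interactions can be parsed in three ways: exposure × period followed by covariates; exposure × covariates; or interactions among all three, which would include covariate × period. The first is the plain reading. The second is effect modification and would not adjust the change. If the third was meant, the proposed wording merely makes it explicit. A condensed article may leave details to an analysis plan, but this one states the terms and the rationale, so what is raised is what it states.

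**Main effects are not always idle.** This stands. If having a reading in a given period depends on a covariate, main effects can remove bias. One simulation had no covariate-related trend, 4–8 mm Hg per SD on BP level, a 0.75 SD imbalance and strongly covariate-dependent availability in uninvited patients. Bias was -0.69, -1.02 and -1.18 without covariates and 0.01, 0.00 and 0.08 with main effects (simulation SE about 0.045). With availability at random they made no difference. That is a different bias from the trend bias at issue here.

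**The list itself is sensible.** This stands too. Age, frailty, deprivation and medication may well predict both invitation and BP change. A reader might infer from the wrong rationale that the covariates are the wrong ones; the document does not support that.

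**Subgroups offer some protection.** The modelling is repeated by sex, cardiovascular history, baseline BP, deprivation, ethnicity and area, where trend differences could show. These analyses are exploratory, omit age and frailty, and do not correct the primary estimate.

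**Conclusion.** The point holds in a limited form and should be fixed. The stated rationale concerns an association that the study does not estimate. On the plain reading, the patient-level covariates leave bias from differential BP trend essentially untouched: exactly so with balanced readings, and nearly so on average with uneven ones. That result follows from the model's form. The size does not: 0.5–2 mm Hg against a planned -3 rests wholly on the assumed 0.5–1 SD imbalance and 1–2 mm Hg per SD, for which the documents give no figure.

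A reader might go further and call the primary effect unadjusted. The documents do not support that: the home/clinic term adjusts the contrast, exposure × period removes stable level differences, and main effects can help when availability of readings depends on covariates. Nor do they support the inference that patients with a missing covariate will be dropped, since the article does not say how missing covariates are handled. And because the bias is assumed and the sentence ambiguous, the point does not show that the primary result will be invalid.

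**What to change.** In Statistical analysis, state that covariates are chosen as predictors of invitation and of BP change, and that each listed patient-level covariate enters with its interaction with period. Alternatively, use overlap weights from a within-practice propensity model for invitation on the same covariates; this also gives little weight to uninvited patients who would hardly ever be invited.

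Baseline SBP and DBP need separate handling, because the baseline value may also be one of the before-period outcome readings. The text should say how the two are kept apart, or model after-period BP given before-period BP.

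The cost is wording and about a dozen parameters: five demographic, three clinical other than BP and three history variables make eleven, with more for multi-category ones. At 1:1 allocation the standard error rises by a factor of √(1 + d²/4) per imbalanced covariate: √1.0625 = 1.031 at d = 0.5 and √1.25 = 1.118 at d = 1, so roughly 3–12%. In the balanced simulation, adding the driving covariate with its period interaction raised the SD of the estimate from 0.696 to 0.760, or 9%.
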